***Procedures***

*Informed Consent*

The subject (or witness if illiterate) or the parent or guardian of a minor must personally sign and date the latest approved version of the informed consent form before any study specific procedures are performed. Written and verbal versions of the participant information and informed consent in the local language will be presented to the participants detailing no less than: the exact nature of the study; the implications and constraints of the protocol; the known side effects and any risks involved in taking part. It will be clearly stated that participation is voluntary and that the participant or guardian is free to withdraw from the study at any time for any reason without prejudice to future care, and with no obligation to give the reason for withdrawal.

Written informed consent will be obtained by means of participant or guardian dated signature or thumb print (if unable to write) and dated signature of the person who presented and obtained the informed consent.

*Screening, Eligibility and Baseline Assessments*

Patients who present at the participating sites will be screened to assess eligibility. Full consent/assent will be obtained before any enrolment procedures are conducted. It will be made clear from the outset that refusal to participate will not jeopardize subsequent antimalarial treatment.

*Demographics and Medical History*

Basic demographic and epidemiological data (e.g. sex, age, address, prior treatment and a full medical history) will be recorded by the study staff.

*Physical Examination and Vital Signs*

Physical examination will be conducted by a qualified investigator. Weight, pulse, blood pressure, respiratory rate, temperature, spleen and liver size will be recorded.

*Drug history*

All prescribed or over-the-counter and traditional medications used within the last 7 days will be recorded. Any drug allergies will be recorded.

*Screening blood & urine tests*

- A parasite count from Giemsa stained thick and thin blood films
- Full blood count or haematocrit
- G6PD spot test

*Randomisation and blinding*

Subjects who fulfil all the inclusion criteria and have none of the exclusion criteria will be randomised 1:1;1 to one of the three treatment arms. Allocation will be done by drawing the next sequential numbered opaque envelope, which contains the study number of the patient referring to the study treatment. The subjects will be assigned a study arm through a computer-generated randomisation scheduleThis is an open-label study so the blinding of investigators and patients is not applicable. However, the randomisation procedure allows for adequate drug allocation concealment before envelopes are opened. All laboratory investigations will be performed without knowledge of the treatment allocation.

*Blood sampling*

On admission

On study admission, immediately before drug administration, blood will be collected for the following:

- parasite count
- EDTA 2mL whole blood sample for PCR parasite genotyping
- haematocrit

G6PD spot test

*Study drug regimens*

(1) chloroquine (25mg base /kg total) only

(2) chloroquine (25mg base /kg total) followed by primaquine 0.25mg base/kg/ day for five days

(3) chloroquine (25mg base/kg total) followed by primaquine 0.25mg base/kg/ day for 14 days

*For recurrences:*

chloroquine (25mg base /kg total) followed by primaquine 0.25mg base/kg daily for 21 days.

The first dose will be observed but all subsequent antimalarial doses will be taken at home. Each patient will be instructed on the need to complete the full course of treatment.

*Follow up procedures*

Patients will be seen daily until a febrile then weekly for one month and thereafter every one to two months for 15 months. If vivax malaria recurs blood will be taken for parasite genotyping and comparison with the original infection.

*Additional visits*

Patients presenting to the clinic with a fever or other symptoms on unscheduled days will be assessed by the study physician. Their temperature will be recorded and blood smear will be made for any patient with a documented fever (oral or tympanic temperature ≥ 37.5˚C) or a history of fever. Patients will be treated as clinically indicated.

Patients with recurrent parasitaemia

Patients with a recurrent parasitaemia during follow up will have blood taken for the following:

- parasite speciation and count
- haematocrit
- if parasitaemic: EDTA 2mL whole blood sample for PCR parasite genotyping

*Discontinuation/ Withdrawal of Participants from the Study*

Each participant has the right to withdraw from the study at any time. In addition, the investigator may withdraw a participant if he or she considers it necessary for any reason including:

- Significant non-compliance with study requirements
- An adverse event which requires discontinuation of the study medication or results in inability to continue to comply with study procedures
- Disease progression which requires discontinuation of the study medication or results in inability to continue to comply with study procedures
- Blood transfusion
- Development of severe malaria
- Loss to follow up

If an individual is prematurely discontinued from study treatment for any reason, the investigator will make every effort to perform the following evaluations: physical examination and vital signs assessment, haematocrit level, parasite count and AE assessment. The reason for withdrawal will be recorded in the CRF. If the subject is withdrawn due to an adverse event, the investigator will arrange for follow-up visits until the adverse event has resolved or stabilised.

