**TRIAL DESIGN**

Study sites

*Summary of Trial Design*

This will be a prospective open label comparison of chloroquine (CQ) alone versus CQ plus 5 days unobserved primaquine or CQ plus 14 days unobserved primaquine in patients with acute vivax malaria in Kolkota. Patients will be followed for 15 months and primary and recurrent infections were genotyped.

Study duration; **2 years**

*Primary and Secondary Endpoints*

Primary Endpoint

Recurrence rate of vivax malaria over 15 months

Secondary Endpoints

Parasite clearance time assessed by microscopy

Fever clearance time (i.e. the time taken for the tympanic temperature to fall below 37˚C and remain there for at least 24 hours)

Genotype assessments Parasite clearance time assessed by microscopy

*Trial Participants*

Overall Description of Trial Participants

Male and non-pregnant female patients aged between 36 months and 65 years with acute uncomplicated vivax malaria are the target study population. All study patients must meet the applicable inclusion and exclusion criteria.

I*nclusion Criteria*

- Male or female, aged from 36 months to 65 years old, inclusive
- Acute uncomplicated *P. vivax* malaria, confirmed by positive blood smear with asexual forms of *P. vivax*
- Fever defined as > 37.5°C tympanic temperature or a history of fever within the last 24 hours
- Written informed consent (by legally acceptable representative in case of children)
- Willingness and ability of the patients/guardians to comply with the study protocol for the duration of the study

*Exclusion Criteria*

- Signs of severe/complicated malaria (WHO, 2000)
- Haematocrit < 25% or haemoglobin (Hb) < 8 g/dL at enrollment
- Acute illness other than malaria requiring treatment
- For females: pregnancy, breast feeding
- Patients who have received antiamalrial treatment within the previous 7 days
- History of allergy or known contraindication to study drugs
- G6PD deficiency;patients who are deficient on spot testing will not be allocated to the two primaquine groups.

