**STUDY DRUGS**

Storage of Study Drugs

All efforts will be made to store the study drugs in accordance with the manufacturers' recommendations in a secure area.

Compliance with Study Drugs

Only the first dose will be administered as Directly-Observed-Therapy. If the patient vomits, and is re-dosed; this will be recorded in the CRF. This is an effectiveness not an efficacy study.

Concomitant Medication

Throughout the study, investigators may prescribe any concomitant medications or treatments deemed necessary (e.g. antipyretics or anti-emetics) to provide adequate supportive care except for antibiotics with antimalarial activity unless unavoidable (e.g. doxycycline, azithromycin). If these are required the patients will be kept in the study and this will be noted as a protocol deviation.

Antimalarials for recurrent infections (see Rescue treatment) and non-falciparum malaria (if applicable) will be prescribed as described above. Any medication, other than the study medication taken during the study will be recorded in the CRF.

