**SAFETY REPORTING**

This trial will be using standard drugs that have either been registered for decades and evaluated extensively. Therefore, the safety aspects of this trial will be limited to close observation while patients are in hospital, treating any intercurrent illnesses or drug-related side effects and recording and reporting only serious adverse events.

Definitions

*Adverse Event (AE)*

In this study, an AE is either a drug-related side effect or a new or exacerbation of a pre-existing symptom, sign or illness (other than malaria).

Serious Adverse Event

*A serious adverse event is an AE that:*

results in death

is life-threatening i.e. the patient was at risk of death at the time of the AE

requires inpatient hospitalisation or prolongation of existing hospitalisation

results in persistent or significant disability/incapacity or

is a congenital anomaly/birth defect

requires acute medical or surgical care to prevent one of the outcomes listed above

Reporting Procedures for Serious Adverse Events

All SAEs will be reported by the site investigator to the Medical Monitor, [name], or his designee, within one day of his or her awareness of the SAE..

The site investigator must also report the SAEs to the local ethics committee in accordance with local requirements.

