**ETHICS**

Declaration of Helsinki

The Investigator will ensure that this study is conducted in compliance with the Declaration of Helsinki

ICH Guidelines for Good Clinical Practice

The Investigator will ensure that this study is conducted according to any National Regulations and that it will follow the principles of the ICH Guidelines for Good Clinical Practice 1996.

Approvals

The study protocol and its associated documents will be submitted to the appropriate local ethics committees for written approval.

The Investigator will submit and, where necessary, obtain approval from the above parties for all substantial amendments to the original approved documents.

Risks

This study will use drugs that have been studied thoroughly and their toxicities are well described. In general, they are all well tolerated.

Benefits

Benefits of Treatment

Malaria is a disease that needs to be treated promptly. All patients will benefit from receiving efficacious treatment at no cost. They will be followed up closely and will be given rescue treatment if clinically indicated.

Alternatives to Study Participation

Subjects are able to decline freely participation in this study. If so, they will receive standard care for their malaria.

Confidentiality

The trial staff will ensure that the participants’ anonymity is maintained. All documents will be stored securely and be accessible to trial staff and authorised personnel only.

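### Every recurrence is treated with 21 days of primaquine, with no pregnancy check or exception, and the screening list names no urine test to support the pregnancy exclusion

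*Protocol*

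**What the plan says.** **Entry.** The Synopsis and the Exclusion Criteria under Trial Design both exclude "For females: pregnancy, breast feeding". Trial Design describes the target population as "Male and non-pregnant female patients aged between 36 months and 65 years", so women of childbearing age are enrolled.

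**Screening.** Under Procedures, the heading "Screening blood & urine tests" is followed by three items: a blood-film parasite count, a blood count or haematocrit, and a G6PD test. The admission samples listed under Blood sampling add a genotyping sample but no urine or pregnancy test.

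**Recurrence.** Study drug regimens, For recurrences, gives one treatment: "chloroquine (25mg base /kg total) followed by primaquine 0.25mg base/kg daily for 21 days". It is not limited by arm, sex or pregnancy. Concomitant Medication, under Study Drugs, confirms it: "Antimalarials for recurrent infections (see Rescue treatment) and non-falciparum malaria (if applicable) will be prescribed as described above".

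**Discretion.** Additional visits says "Patients will be treated as clinically indicated". Benefits of Treatment, under Ethics, says "They will be followed up closely and will be given rescue treatment if clinically indicated". The withdrawal section lets the investigator withdraw a participant for any reason. Its listed examples do not include pregnancy.

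**Safety reporting.** A serious adverse event includes one that "is a congenital anomaly/birth defect".

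**The concern.** Being non-pregnant at entry says little about a woman's status at a recurrence up to 15 months later. The retreatment rule takes no account of this. It applies the same 21-day primaquine course to everyone, including patients randomised to chloroquine alone who had no primaquine at entry. A site that follows the rule and the listed recurrence tests exactly could give primaquine to a woman in early, unrecognised pregnancy.

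At entry, the heading suggests that a urine test was intended, but the list does not contain one. What is at stake is patient safety. The protocol chose not to enrol pregnant women, and it counts a birth defect among its serious adverse events. Eligibility tests and retreatment rules belong in the protocol, so a separate analysis plan would not be expected to supply them.

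**Working it through.** No figure in the protocol bears on this point, so the check sets the relevant sections side by side.

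**1. Entry tests against entry criteria (Procedures; Trial Design).**

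| Screening item | Criterion it serves | Urine test? |
|---|---|---|
| Parasite count on films | Vivax malaria confirmed by smear (inclusion) | No |
| Blood count or haematocrit | Anaemia exclusion | No |
| G6PD test | G6PD exclusion | No |

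Urine tests listed: 0 of 3. The pregnancy exclusion is left to the medical history and the physical examination.

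**2. Where primaquine is given (Study drug regimens).**

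| Arm | Primaquine at entry | Primaquine at recurrence |
|---|---|---|
| Chloroquine alone | None | 21 days |
| Chloroquine + 5 days | 5 days | 21 days |
| Chloroquine + 14 days | 14 days | 21 days |

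Primaquine is given at entry in 2 of 3 arms and at recurrence in 3 of 3. The daily dose is 0.25 mg base/kg throughout, so the recurrence course totals 21 × 0.25 = 5.25 mg/kg. The randomised courses total 5 × 0.25 = 1.25 mg/kg and 14 × 0.25 = 3.5 mg/kg. The one course with no entry screen close to it is the longest of the three.

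**3. Tests at recurrence (Patients with recurrent parasitaemia).** Three items are listed: species and count, haematocrit, and a genotyping sample. Pregnancy tests: 0 of 3.

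**4. What the discretion clauses cover.** Clinical judgement at unscheduled visits, rescue treatment when indicated, and withdrawal for any reason would each let an investigator withhold primaquine from a woman known or suspected to be pregnant. None of them prompts anyone to look for a pregnancy.

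**5. How often the recurrence rule might apply.** The sample-size section assumes relapse in 30% on chloroquine alone and 4% on 14-day primaquine, with 50 patients per arm. Ignoring loss to follow-up, that is 0.30 × 50 = 15 and 0.04 × 50 = 2 first recurrences. No rate is given for the 5-day arm. If it lies anywhere between the other two, that arm adds 2 to 15, for a total of 15 + 2 + 2 = 19 to 15 + 2 + 15 = 32. This counts both sexes and all ages and leaves out reinfections and second recurrences. It shows the scale of retreatment, not the number of pregnancies. The protocol gives neither the share of females of childbearing age nor the frequency of pregnancy, so the number exposed cannot be derived.

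**The case against.** Several stronger readings are tempting, and the protocol does not support them.

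- *A pregnant woman would be given primaquine.* The discretion and withdrawal clauses allow an investigator to avoid this whenever pregnancy is known or suspected. The supportable word is could, and the risk that remains is unrecognised pregnancy.
- *The trial bars primaquine in pregnancy and then prescribes it.* The exclusion keeps pregnant women out of the whole trial, including the chloroquine-only arm. Where the protocol wants a restriction on primaquine alone, as for G6PD deficiency, it says so. It nowhere states that primaquine is unsafe, or chloroquine safe, in pregnancy. The recurrence rule is therefore a gap and not a contradiction.
- *An exposed pregnancy would never come to light.* Visits are weekly for a month and then every one to two months. A pregnancy would often become evident in that time, and the serious adverse event definition gives a route for reporting a birth defect.
- *Sites would not test at screening.* Other exclusions, such as breast feeding, allergy and recent antimalarial use, also rest on history. The heading suggests that a urine test was intended and its list entry dropped.

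All four objections stand, and they narrow the point. They do not close it. History and clinical judgement can miss an early pregnancy, no listed step looks for one, and the retreatment rule as written makes no exception.

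**Conclusion.** The point holds as a patient-safety gap that is cheap to close. Its main part is the retreatment rule: 21 days of primaquine for every recurrence, in all three arms, over 15 months, with no pregnancy check or exception. Its smaller part is the screening list, which announces urine tests and names none, so an early pregnancy could be randomised to either of the two primaquine arms.

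The conclusion rests on the text alone, plus one assumption: that by excluding pregnant women at entry the protocol meant to avoid exposing pregnancies to trial treatment. The text mismatch is certain. Whether any pregnancy would be exposed is not known. A reader might also infer some bias in the recurrence comparison, but nothing in the protocol supports that and none is claimed.

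**What to change.** 1. **Study drug regimens, For recurrences:** require a urine pregnancy test in females of childbearing age before recurrence primaquine. If it is positive, withhold primaquine, treat the blood-stage infection as clinically indicated (for example with chloroquine alone) and defer radical cure. The choice of drug is a clinical judgement that the protocol does not settle.
2. **Study Drugs, Concomitant Medication:** make the cross-reference on recurrent infections point to this exception.
3. **Procedures, screening tests:** list the urine pregnancy test for females of childbearing age, with the result recorded before the randomisation envelope is opened.

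**Cost.** Three short wording changes. Strips at entry number fewer than 150 among those enrolled, since 150 is the planned total and males and young children are not tested; women screened but not enrolled add some. One further strip is needed per recurrence in a woman of childbearing age. All tests fit existing visits. The downside is a few more screening exclusions, and women who test positive at recurrence wait for radical cure and stay at risk of relapse meanwhile.

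### Daily visits end on fever alone, which does not fit the parasite and fever clearance endpoints

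*Protocol*

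**What the plan says.** The secondary endpoints (Trial Design, Primary and Secondary Endpoints, and the Synopsis) include "Parasite clearance time assessed by microscopy" and fever clearance, defined as "the time taken for the tympanic temperature to fall below 37˚C and remain there for at least 24 hours".

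The visit schedule (Procedures, Follow up procedures) reads "Patients will be seen daily until a febrile then weekly for one month and thereafter every one to two months for 15 months". In context, the two words *a febrile* mean *afebrile*. The term is not defined, and no assessments are listed for the daily, weekly or later scheduled visits.

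Films and parasite counts are named in five places:

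- Screening: "A parasite count from Giemsa stained thick and thin blood films".
- Admission: "On study admission, immediately before drug administration, blood will be collected for the following", a list that includes a parasite count.
- Unscheduled visits (Additional visits): "blood smear will be made for any patient with a documented fever (oral or tympanic temperature ≥ 37.5˚C) or a history of fever".
- Recurrent parasitaemia during follow-up.
- Premature discontinuation of study treatment (Discontinuation/ Withdrawal).

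The first two precede treatment. The other three depend on an event.

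Fever has a threshold in two other places: above 37.5°C for entry, and 37.5°C or more for a smear at an unscheduled visit.

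**The concern.** A clearance time needs repeated observation until the thing being timed has demonstrably cleared. Here one condition, absence of fever, ends close observation for two different endpoints. Parasites need not clear when fever does, so the last daily visit may come before the first negative film. The fever endpoint also has a persistence condition, and a patient released from daily visits at the first normal reading has not been seen to meet it.

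The width of the uncertainty would also depend on when fever ended: patients whose fever settles earliest would have the least precise parasite clearance times. These two endpoints are the ones that serve the secondary objective on clinical and parasitological response, so that objective would rest on coarse or unconfirmed times.

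**Working it through.** The protocol gives no figure for the clearance endpoints, so the check compares the visit calendar with the endpoint definitions.

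**Sample size, for completeness.** The only computed design figure is 50 per arm, from relapse of 30% versus 4%, 80% power and 20% loss. A two-sided 5% comparison of two proportions with continuity correction gives 39 per arm, and 39 / (1 − 0.20) = 48.75, rounded up to 49, close to the stated 50. No clearance time enters this calculation, so the sample size is unaffected.

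**Inputs.** Daily visits until afebrile, then weekly (Follow up procedures). Fever clearance: below 37°C for at least 24 hours (Primary and Secondary Endpoints).

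**Assumptions.** One visit every 24 hours from admission; first weekly visit on day 7, that is 7 × 24 = 168 hours. The protocol does not say from when the weeks are counted.

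**Parasite clearance.** Suppose, favourably to the plan, that a film is taken at every daily visit and at the weekly visit. If the film at the last daily visit is positive and the day-7 film is negative, clearance lies somewhere in an interval of length 168 − (hour of last daily visit):

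| Last daily visit | Interval to next scheduled visit | In days | With daily films continued |
| --- | --- | --- | --- |
| 24 h | 168 − 24 = 144 h | 6 | 24 h |
| 48 h | 168 − 48 = 120 h | 5 | 24 h |
| 72 h | 168 − 72 = 96 h | 4 | 24 h |

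If the weeks are counted from the last daily visit instead, the interval is 168 hours, or 7 days, in every row. If no film is taken at these visits, there is no interval to compute.

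**Fever clearance.** The result depends on what *afebrile* means:

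| Meaning of *afebrile* | What is observed by the last daily visit |
| --- | --- |
| Below the 37.5°C threshold used elsewhere | A patient at 37.0 to 37.5°C can leave daily visits without having fallen below 37°C |
| First reading below 37°C | The fall is placed within 24 h, but its persistence is not seen. For first readings at 24, 48 or 72 h, confirmation is due at 48, 72 or 96 h; the next visit is at 168 h, which is 144, 120 or 96 h after the last reading |
| The endpoint's own definition | Daily visits run through the confirming reading; clearance is known to about 24 h |

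The first two readings leave the endpoint unconfirmed; the third does not. Even under the third, the stop rule ignores parasites. A patient first below 37°C at 24 h would have a last daily visit at 48 h, and the parasite interval would be 120 h instead of 144 h.

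**The case against.** The best defence is that the protocol leaves visit content unspecified and does not rule films out. This stands. A reader might infer that no post-treatment film is planned and that parasite clearance cannot be measured at all. The text does not support that: the endpoint is stated to be assessed by microscopy, which presupposes films, and the smear rule under Additional visits covers unscheduled days only. The point above therefore grants films at daily visits and rests on the stop rule.

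Second, *afebrile* may mean the endpoint's own 24-hour definition, the only description of resolved fever in the document. No sentence applies 37.5°C to the stop rule. This also stands, so it would be too strong to say that fever clearance cannot be measured.

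Third, a reader might go on to the primary endpoint and infer that recurrence will be detected differently by arm, because the trial is open-label and later visits are one to two months apart. The documents do not show this. The schedule is worded identically for all arms, laboratory work is done without knowledge of allocation, and nothing indicates different attendance. Nor is the handling of patients enrolled on a history of fever alone a fault here, since an analysis plan commonly settles who enters a fever-clearance analysis.

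Fourth, all arms receive the same chloroquine, with primaquine given afterwards, so early clearance bears little on the comparison of 5 with 14 days. That limits the importance of the point but does not remove the mismatch.

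The mention of observation in hospital under Safety Reporting does not answer the point either: it gives no length of stay and no film or temperature schedule, and doses after the first are taken at home.

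**Conclusion.** The point holds as a mismatch between a stated visit rule and two secondary endpoints. For parasite clearance it holds under any meaning of *afebrile*, because the rule never refers to parasites. A patient afebrile but still parasitaemic at the last daily visit has a clearance time known only to within about a week: 4 to 6 days for last daily visits at 72 to 24 hours with a day-7 visit, or 7 days if the weeks start at the last daily visit. For fever clearance it is conditional: under two of the three readings the 24-hour condition is not observed, and under the third the endpoint is measurable to about a day.

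The figures assume one visit per 24 hours and, for parasites, films at every visit. How many patients would be affected cannot be derived from the protocol. The mismatch does not reach the primary endpoint or the sample size. It is worth correcting because the remedy is cheap and no later analysis can recover films or temperatures that were not taken.

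**What to change.** In Follow up procedures, state that a temperature and a blood film are taken at each daily visit, and that daily visits continue until the fever-clearance definition is met (below 37°C for 24 hours) and the film is negative; weekly visits start after that. This settles the meaning of *afebrile* for the schedule and ties the end of daily visits to both endpoints. State also what is measured at the later scheduled visits. The change concerns measurement only and leaves treatment as it is.

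The cost is one or two more early visits and slides for some patients. If that is not feasible, replace the two clearance times by the proportion parasitaemic and the proportion febrile on fixed days, the same for every patient, with a film and a temperature scheduled on those days whether or not fever has gone. That gives up individual clearance times but yields endpoints that the schedule can deliver.

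### Investigators who know the arm may withdraw patients from the study for non-compliance, with no recurrence follow-up to 15 months secured, in a trial declared to measure effectiveness

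*Protocol*

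**What the plan says.** **Withdrawal.** Under Procedures, in Discontinuation/ Withdrawal of Participants from the Study, the protocol states that "the investigator may withdraw a participant if he or she considers it necessary for any reason including" a list of grounds. The list opens with "Significant non-compliance with study requirements" and also contains "Development of severe malaria", blood transfusion and loss to follow-up. Adverse events and disease progression are grounds when they force study medication to stop or prevent further participation.

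The section then turns to early stopping of study treatment and provides for one set of checks: examination and vital signs, haematocrit, parasite count and adverse events. The only later visits it promises are these: "If the subject is withdrawn due to an adverse event, the investigator will arrange for follow-up visits until the adverse event has resolved or stabilised".

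**Design.** Study Drugs, under Compliance, states "This is an effectiveness not an efficacy study". Trial Design describes an open-label comparison of chloroquine alone with "CQ plus 5 days unobserved primaquine or CQ plus 14 days unobserved primaquine". Under Study drug regimens, "The first dose will be observed but all subsequent antimalarial doses will be taken at home". The primary endpoint is "Recurrence rate of vivax malaria over 15 months".

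**A contrast.** Study Drugs, under Concomitant Medication, keeps patients who need antibiotics with antimalarial activity in the study and records a protocol deviation.

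**The concern.** When courses are taken unobserved and the aim is effectiveness, patients who do not finish belong in the result. The longer course may prevent more relapses when completed but be completed less often, and the primary comparison should reflect both. A rule that lets non-compliant patients leave the study can move the estimate towards the effect in those who complied.

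Three features add weight:

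- The investigator knows the arm.
- Opportunity for missed primaquine differs by design: none with chloroquine alone, 5 days in one arm, 14 in the other.
- Study primaquine ends after at most 14 days but the endpoint runs to 15 months, so stopping drug early is no reason to stop observing. The Background itself warns that relapse is underestimated when follow-up ends too soon, and describes temperate-zone relapses at 7 to 10 months. A patient withdrawn in the first weeks would leave before that window.

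A statistical analysis plan can define populations and censoring rules. It cannot supply recurrences that nobody looked for.

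**Working it through.** **1. The plan's own figure.** Statistical considerations assumes 30% relapse on chloroquine alone and 4% on 14-day primaquine, 95% confidence (taken as two-sided 5%), 80% power and 20% loss. The two-proportion formula with continuity correction gives 39 per arm, and 39/(1 − 0.20) = 48.75, rounded up to 49. The stated 50 is consistent with its inputs and is not in dispute. It neither supports nor refutes this point.

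**2. The passages side by side.**

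| Topic | Protocol text | Consequence |
|---|---|---|
| Aim | Effectiveness; only the first dose observed | Incomplete adherence is part of the effect |
| Non-compliance | Discretionary ground for leaving the study | Such patients may be removed |
| Antibiotic with antimalarial activity | Patient stays; deviation recorded | Opposite handling of another deviation |
| After withdrawal | One set of checks; further visits only after an adverse event | 15-month endpoint not secured |

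The withdrawal section passes from leaving the study to stopping study treatment without distinguishing them.

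**3. Illustration of size.** Let c be the recurrence risk in completers, m the risk in non-completers and q the proportion not completing.

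- Risk with everyone followed: (1 − q)c + qm.
- Risk if every non-completer is withdrawn before recurring: c.
- Change in the 5- versus 14-day difference caused by withdrawal: q14(m14 − c14) − q5(m5 − c5).

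Inputs: c14 = 4% and m5 = 30% borrow the protocol's planning rates for the 14-day and chloroquine-only groups. Applying them to completers and non-completers is an assumption. c5 = 15%, q5 = 10% and q14 = 30% are assumptions with no source in the protocol. m14 is varied from 30% (as if no primaquine had been taken) to 15% (as if the 5-day course had been completed, since the daily dose is the same).

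| | m14 = 30% | m14 = 15% |
|---|---|---|
| 5-day, all followed | 0.9 × 15 + 0.1 × 30 = 16.5% | 16.5% |
| 14-day, all followed | 0.7 × 4 + 0.3 × 30 = 11.8% | 0.7 × 4 + 0.3 × 15 = 7.3% |
| True difference | 4.7 points | 9.2 points |
| Difference, all non-completers withdrawn | 15 − 4 = 11 points | 11 points |
| Shift | 6.3 points | 1.8 points |

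Check by the formula: 0.3 × 26 − 0.1 × 15 = 6.3, and 0.3 × 11 − 0.1 × 15 = 1.8.

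**4. If only half of the non-completers are withdrawn.** The 5-day risk becomes (0.9 × 15 + 0.05 × 30)/0.95 = 15.8%. The 14-day risk becomes (0.7 × 4 + 0.15 × 30)/0.85 = 8.6%, or (0.7 × 4 + 0.15 × 15)/0.85 = 5.9%. The differences are 7.2 and 9.8 points, shifts of about 2.5 and 0.6 points.

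**5. Direction.** In these cases the shift favours the longer course. The sign depends on q14(m14 − c14) exceeding q5(m5 − c5), and the protocol gives none of these quantities for completers and non-completers.

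**The case against.** The strongest reply is that the text does less than a reader might infer.

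- **That failures are removed selectively.** The rule is discretionary, and its wording concerns study requirements, which could mean missed visits in any arm. Only the first dose is observed and no later adherence measure is described, so investigators might not identify most non-completers. This stands: the rule permits selective removal but does not show that it would happen.
- **That the trial would overstate the 14-day advantage by a known amount.** The 4% is a planning rate for a whole arm with unobserved dosing, not a rate in completers, and the other key inputs are assumed. A patient who stops a 14-day course after day 5 has taken at least the 5-day course, so giving all such patients the 30% no-primaquine rate is an extreme. This stands too, which is why 4.7 against 11 points is only the worst end of an illustration.
- **That severe malaria is taken out of the endpoint.** The protocol does not say so. Any recurrent parasitaemia is to be speciated, counted and genotyped, so a severe vivax recurrence would be documented when detected, and later withdrawal does not erase it. Severe malaria could also arise in the initial illness or from another species. How such cases are counted may properly be left to the analysis plan.
- **That all observation stops at withdrawal.** The one-off checks are tied to stopping study treatment, and the text does not say that recurrence visits cease.

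What the reply leaves untouched is that, for patients withdrawn from the study for non-compliance, nothing says recurrence visits continue.

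**Conclusion.** The point holds in limited form. The withdrawal section allows an arm-aware investigator to end study participation for non-compliance, among other reasons, without securing recurrence follow-up. That is at odds with the declared effectiveness aim and with a primary comparison of unobserved courses. Arm-related informative censoring is possible rather than established, but endpoint data lost this way are beyond repair by any analysis plan.

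No size or direction of bias follows from the protocol. With the assumed inputs and every non-completer withdrawn, the difference would be inflated by 1.8 to 6.3 points. If fewer are withdrawn the shift is smaller, and if the rule is never used for missed doses this route adds no bias.

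**What to change.** Reconcile the withdrawal section with the effectiveness statement under Study Drugs:

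1. Distinguish stopping study drug from leaving follow-up.
2. State that all randomised patients are followed for recurrence to 15 months in their assigned arm, whatever their adherence or early stopping of study drug. Only withdrawn consent or actual loss to follow-up ends observation.
3. State that a vivax recurrence that leads to withdrawal, including a severe one, counts as an event. At the planning rate the 14-day arm expects 0.04 × 50 = 2 events, so the status of even one should not be left open.

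None of this alters how a patient is treated or when study drug is stopped.

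The cost is protocol wording plus continued routine visits, on the existing schedule, for patients who would otherwise have been withdrawn. At the illustrative rates that is up to 0.1 × 50 + 0.3 × 50 = 20 of the 100 primaquine patients.
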